## Abstract

**Background:**

Multiple sclerosis (MS) is one of the world’s most common neurologic disorders leading to severe disability in young adults. MS-related fatigue directly impacts on the quality of life and activity levels of people with MS. Self-management strategies are used to support them in the care of their health. Mobile health (mHealth) solutions can offer tools to help symptom management. Following a user-centered design and evidence-based process, an mHealth solution called More Stamina was created to help persons with MS manage their fatigue.

**Objective:**

The overall study aims are to explore the feasibility, acceptability, and usability of More Stamina, a mobile app for fatigue self-management for persons with MS.

**Methods:**

A mixed-methods, multicenter study will be used to assess the feasibility, acceptability, and usability of More Stamina. The study will take place during the third and fourth quarters of 2020 (Q3-Q4 2020) in 3 locations: Argentina, Spain, and Switzerland. A longitudinal cohort study will take place, and think-aloud protocols, open-ended interviews, and short answer questionnaires will be used. Persons with MS will be recruited from the different locations. This study seeks to enroll at least 20 patients that meet the criteria from each site for the longitudinal cohort study (total n=60).

**Results:**

Ethical approval has been granted in Argentina and is pending in Spain and Switzerland. Outcomes will be published in peer-reviewed medical journals and presented at international conferences.

**Conclusions:**

Findings from this study will be used to help understand the role that mHealth can play in fatigue management in MS.

**Trial Registration:**

ClinicalTrials.gov NCT04244214; https://clinicaltrials.gov/ct2/show/NCT04244214

**International Registered Report Identifier (IRRID):**

PRR1-10.2196/18196

## Introduction

### Background

Multiple sclerosis (MS) is one of the world’s most common neurologic disorders leading to severe disability in young adults. More than 2.3 million people live with MS in the world, with higher incidences in Northern Europe and in temperate climates [1]. MS is a chronic condition with high self-management needs [2] that require significant support [3-5] since the majority of self-management occurs at home [6]. MS symptoms range from simple visual disturbances and altered sensation to severe fatigue and cognitive problems with mobility issues [2]. Persons with MS can also go through stretches of periods in which symptoms worsen, called “attacks” or “relapses” [1,2]. Fatigue is the most common and disabling symptom of MS, affecting up to 80% of patients [7-12]. There seems to be some association between MS fatigue and environmental conditions such as the time of the day and weather [13] but it is still unknown how much of an influence these factors have. MS fatigue has a huge impact on quality of life [8,9] and socioeconomic status for persons with MS and is the major reason for early retirement [14]. As a result of MS, persons with MS are typically less active [15] and have reduced levels of physical activity [16-18].

Mobile health (mHealth) is the delivery of health care or health care–related services through the use of portable devices [19]. The use of mHealth software apps has grown in recent years, to the point where commercial app stores hold thousands of health care–related apps [20]. Several digital and remote communication technology apps have been developed for MS clinical monitoring and management, to complement traditional clinical approaches [21]. Wearable devices, including actigraphy, gyroscopes, and body temperature or heart rate monitors, have been used to obtain a more comprehensive assessment of different body functions and to monitor disability in persons with MS [22]. A recent review [21] showed that the use of apps for MS as complements to traditional in-clinic care can improve outcomes and increase access to care, disease information, and support. The use of mHealth could help persons with MS to be more active in their self-management, for example, by tracking adherence to treatment, changes in bladder and bowel habits, and activity and mood.

However, digital health technologies have low adoption rates by patients with chronic diseases, in part explained by an inappropriate fit of these technologies with patients’ daily lives and the high patient burden associated with digital self-monitoring [23]. Studies regarding the attitudes of persons with MS toward using smartphone apps highlight the benefits of tailoring apps to specific patient needs [24,25]. Further, involving patients and health care professionals in the design of technology is a need that has been often raised [26-32] and could be helpful in increasing adoption rates [33-35].

In previous studies, we explored available mHealth apps for persons with MS and found that only a handful exist [31,36]. This prompted the user-centered design (UCD) process of an mHealth solution specifically tailored for this target population called More Stamina.

### User-Centered Design

UCD is a design philosophy that places the needs and characteristics of end users in the center of software design and development [37-39]. Through the use of UCD, solutions that are specific to the characteristics of the intended users are designed with higher acceptance and fewer user errors [38-40]. The overall process of UCD comprises the specification of the context of use (understand users and their characteristics and environment), specification of the requirements (identify the granular requirements and needs), production of solutions (start an iterative process of design and development), and evaluation (testing to find critical feedback on the product) [37,41].

The evaluation of usability entails a wide array of methodologies that vary in terms of research design, complexity, cost, and duration [42]. Different methods can be used to evaluate a system design on its usability, such as expert-based inspections and user-based testing [43]. Following UCD ensures that mHealth apps are more likely to meet end user needs and expectations [44,45].

### More Stamina

More Stamina is a gamified task organization tool designed to help persons with MS manage their energy, to minimize the impact of fatigue on their daily life. The tool acts as a to-do list where users can input the tasks they want to accomplish that day in a simple manner (Figure 1). More Stamina is currently available in English, Spanish, Finnish, and German.

The overall concept is that a person’s energy is represented through a visual metaphor (progress bar) and a symbolic unit that quantifies the amount of estimated effort a given activity might take (Stamina Credits). Users start their day with 100 Stamina Credits and assign them to new activities for that day. As users go through their day and complete the activities, they mark them as done, and the system prompts them to assess whether their effort was underestimated, overestimated, or properly estimated. More Stamina keeps track of these answers as data points and starts analyzing and creating a trend for each activity (eg, “shopping”). Repeated use of More Stamina allows it to learn about the user’s habits, and once sufficient information is gathered on “shopping,” a recommendation feature starts reminding users of their own tendencies.

The app logs user activity through the in-built sensors of the device and is able to monitor the number of steps, walking pace, distances, and GPS positioning. Patient-reported outcomes are available and optional in More Stamina. Standardized tools such as the Fatigue Severity Scale [46] and Chalder Fatigue Scale [47] are loaded into the system. Usage statistics are gathered locally for each added activity to keep track and collect assessments; the user can choose to share these statistics to a secure server for analysis. Users have control as to which information to disclose and with whom, whether it’s personal, clinical, or treatment-related. Additionally, they can opt-in to send de-identified information for research purposes.

**Figure 1 figure1:**
[figure not shown]
More Stamina screenshots.

### Current Status

The More Stamina app was created following the UCD approach through iterative development, allowing continuous improvement of the app. The progress of the solution through the different phases of the UCD process is reported in our previous studies. The state of the practice of health apps for MS was studied through a systematic app review [31,36]. The needs, barriers, and facilitators of mHealth apps for persons with MS were explored using focus groups and interviews [25]. User profiles, or “personas,” were created to aid the design process [25,48], and the design process, prototyping, and initial usability testing have been described [49].

The work intended in this phase will assess the feasibility, acceptability, and usability of the mHealth solution with persons with MS (see Figure 2).

**Figure 2 figure2:**
[figure not shown]
Phases of the user-centered design for the More Stamina app. The green boxes indicate the areas of focus for the current study. mHealth: mobile health; MS: multiple sclerosis.

### Objectives

The overall study aims are to explore the feasibility, acceptability, and usability of More Stamina, a mobile app for fatigue self-management for persons with MS.

The specific objectives are to estimate adherence to the use of More Stamina; estimate the effect of More Stamina adherence on behavior change, measured through changes in the amount of activities and amount of estimated energy per activity; estimate the effect of adherence to the use of More Stamina on the perception of fatigue management; validate the value proposition of More Stamina; identify More Stamina user activity patterns of persons with MS; and identify factors associated with the use of More Stamina.

## Methods

### Study Design

A mixed-methods, multicenter study will be used to assess the feasibility, acceptability, and usability of More Stamina. The study will take place during the third and fourth quarters of 2020 (Q3-Q4 2020) in 3 locations: Argentina, Spain, and Switzerland.

A longitudinal cohort pilot study will be conducted using a series of well-established standardized tools for user-based evaluations and surveys (see Standardized Tools). Participants’ background information regarding health information, quality of life, and familiarity with mobile technologies will be collected. Potential cultural differences will also be explored through qualitative approaches. System usage logs will quantify patient engagement with the system [50].

### Settings

This study is part of a collaborative project between researchers and different institutions across the globe. The work will take place in 3 locations with local teams. Sessions will be conducted by a native language facilitator. Overall study coordination will be carried out by [name] from the University of Oulu as part of the More Stamina research project.

#### Argentina

Hospital Italiano de Buenos Aires (HIBA) is a university general hospital in the Autonomous City of Buenos Aires that includes 2 hospitals (Central Hospital and Hospital Italiano de San Justo Agustin Rocca) and 22 primary care centers. This organization has 750 beds, conducts approximately 2.5 million outpatient visits per year, and includes a health maintenance organization that delivers prepaid health care to approximately 150,000 members per year.

The Argentinian local team will be composed of researchers from HIBA.

#### Spain

The Vithas Nisa Sevilla Hospital (VNH) ranks as the number one private center in Andalusia and fourth in all of Spain with a specialized unit aimed at researching and treating MS. This unit is composed of a multidisciplinary team, including neurologists, neuropsychologists, physical therapists, clinical researchers, nurses, and administrative staff.

The Universidad de Sevilla is the main house of learning in the Andalusian province of Spain and provides superior education by means of studies, teaching, and research, as well as the generation, development, and diffusion of knowledge to serve citizens and society.

The Spanish local team will be composed of researchers from the Universidad de Sevilla and VNH.

#### Switzerland

Kliniken Valens is a center specializing in neurological rehabilitation services located in Valens, Switzerland. Kliniken Valens employs a multidisciplinary staff, including neurologists, physiotherapists, occupational therapists, speech therapists, and sports therapists. In 2019, a total of 550 persons with MS were admitted for neurological rehabilitation, of which 70% suffered from fatigue and this was the primary focus of their stay.

The Swiss local team will be composed of researchers from Kliniken Valens and the University of Oulu.

### Recruitment and Sample Size

Persons with MS will be recruited from patient databases at HIBA, VNH, and Kliniken Valens and invited to participate in the study. Inclusion criteria will require each participant to be >18 years old, have received a confirmed MS diagnosis according to McDonalds criteria [51] at least 1 year prior to the study, have none to moderate physical disability (Expanded Disability Status Scale [EDSS] <6.5) at the time of recruitment, have no major cognitive or haptile impairment influencing the ability to use the app, be fluent in one of the languages in which More Stamina is available, and be the owner or user of a compatible smartphone device with internet access.

Exclusion criteria include refusal to participate, cognitive or physical impairment that prevents the use of mobile phones, and inability to attend the follow-up encounters.

This study seeks to enroll at least 20 patients that meet the criteria from each site for the longitudinal cohort study (total n=60). The sample size is an adequate number because of the methods used that provide extensive, detailed data [52].

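### Fatigue is not required at entry and baseline fatigue has no stated role in the analysis, so results for a fatigue app may pool people with and without the problem it addresses

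*Protocol article*

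**What the plan says.** Under Recruitment and Sample Size, the protocol article sets entry by age and diagnosis ("Inclusion criteria will require each participant to be >18 years old, have received a confirmed MS diagnosis according to McDonalds criteria"), by disability ("have none to moderate physical disability (Expanded Disability Status Scale [EDSS] <6.5) at the time of recruitment"), and by cognitive and touch function, language and smartphone access. On the other side, "Exclusion criteria include refusal to participate, cognitive or physical impairment that prevents the use of mobile phones, and inability to attend the follow-up encounters". Neither list mentions fatigue. Participants come from the sites' patient databases, and the target is stated as "This study seeks to enroll at least 20 patients that meet the criteria from each site for the longitudinal cohort study (total n=60").

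The article gives two figures on how common fatigue is. In Background: "Fatigue is the most common and disabling symptom of MS, affecting up to 80% of patients". For the 550 persons with MS admitted to the Swiss site in 2019: "of which 70% suffered from fatigue and this was the primary focus of their stay".

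The Objectives include estimating adherence, estimating the effect of adherence on how fatigue management is perceived, and a further aim to "validate the value proposition of More Stamina". Quantitative Analysis makes change in self-perceived fatigue a regression outcome. It adjusts for age, sex and eHEALS and says that the need for other confounders will be evaluated. Study Flow has every participant complete the Chalder Fatigue Scale at Encounter 1.

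**The concern.** The app's purpose is to reduce the impact of fatigue on daily life. Someone who has MS but little fatigue can satisfy every entry criterion. That person has less reason to use the app, little room for fatigue to improve, and little basis for judging whether the app delivers what it promises.

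If such people are pooled with fatigued users, the mean change in fatigue no longer describes the intended user. A low adherence or acceptability figure could then reflect a weak app or simply a lack of need. The Discussion says this pilot is to lay the foundations for a larger randomized study, so an ambiguous answer would carry forward into that design.

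**Working it through.** **1. Cohort size.** 3 sites × 20 = 60, which agrees with the stated total. The article offers no power or precision calculation to reproduce; its justification is that "The sample size is an adequate number because of the methods used that provide extensive, detailed data".

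**2. Possible number with little fatigue.** Inputs are the 80% in Background and the 70% under Switzerland, applied to 60 on the assumption that the cohort resembles those populations.
- At 80%: (1 − 0.80) × 60 = 12, with a 95% binomial range of 6 to 18.
- At 70%: (1 − 0.70) × 60 = 18, with a range of 11 to 25.
- 80% at two sites and 70% at the Swiss site: 40 × 0.20 + 20 × 0.30 = 14.

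That is about 4 to 6 people per site of 20.

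**3. Mean change in fatigue.** Let f be the fatigued share and D the mean change among fatigued participants. Assume no change in the others. The pooled mean is f × D + (1 − f) × 0 = f × D, that is 0.80 D or 0.70 D. This is arithmetic given the zero-change assumption. The article gives no range for the Chalder scale, so the size of any floor effect cannot be checked.

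**4. Adherence-fatigue slope.** Suppose change = b × use among the fatigued and 0 among the others. Let use have mean m1 and variance V1 in the fatigued, and m0 and V0 in the others. Then:
- covariance = f × V1 × b + f(1 − f)(m1 − m0)(b × m1)
- variance = f × V1 + (1 − f) × V0 + f(1 − f)(m1 − m0)²

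If both groups use the app equally on average (m1 = m0), the between-group terms vanish and the pooled slope is below b whenever V0 > 0.

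If the non-fatigued use it less, the result can go the other way. Illustrative values, all assumed: m1 = 4, SD 2; m0 = 0.5, SD 0.5.
- f = 0.70: covariance = 2.80b + 0.21 × 3.5 × 4b = 5.74b; variance = 2.80 + 0.075 + 0.21 × 12.25 = 5.45; slope = 1.05b.
- f = 0.80: covariance = 3.20b + 0.16 × 3.5 × 4b = 5.44b; variance = 3.20 + 0.05 + 0.16 × 12.25 = 5.21; slope = 1.04b.

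The direction of the bias therefore depends on how use differs between the groups, which is not known in advance.

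**5. Stated use of baseline fatigue.** It is measured at Encounter 1. It is not an entry criterion and not a named covariate. It is not one of the three selection themes for the think-aloud subgroup, which are time since diagnosis, digital literacy and disease burden. No candidate factors for app use are named.

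**6. Precision lost by splitting.** The correlation detectable with 80% power (two-sided 5% assumed, Fisher z) is tanh((1.960 + 0.842)/√(n − 3)). This gives 0.35 for n = 60, 0.39 for n = 48 and 0.42 for n = 42.

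**The case against.** Broad entry is defensible. The article describes its users as persons with MS, wants to identify factors associated with use, and says under Limitations that understanding differences in the importance of fatigue management is part of the aims. A fatigue cut-off at entry would narrow the range of a likely predictor of use. It would also need screening before Encounter 1, because the Chalder scale is completed only after consent. Limitations further disclaims assessment of health outcomes. All of this stands, and it is why restricting entry is not the main recommendation.

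The prevalence figures are also loose. The 80% is a ceiling for MS in general. The Swiss 70% refers to rehabilitation admissions and also mentions the focus of the stay, so the remaining 30% may include fatigued people admitted for other reasons. People who agree to test a fatigue app may be more often fatigued than the databases they come from. A reader might infer that 20% to 30% of this cohort will have no fatigue; the article does not support that as an estimate.

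A reader might also infer that the adherence-fatigue slope must shrink in proportion to the fatigued share. Step 4 shows that this fails as soon as the non-fatigued use the app less, which is the very behaviour one would expect of them.

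Finally, a split by baseline fatigue could sit in an analysis plan that is not shown, and the clause on other confounders leaves room for it. That limits the point to what the article itself fixes: eligibility without fatigue, and a named covariate list without it.

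**Conclusion.** The point holds as a matter of target population and interpretability, not as an error in the sample size. Followed as written, the plan pools people with and without the problem the app addresses. The number affected is unknown: roughly 12 to 18 of 60 if the cohort matches the article's 70% to 80% figures, fewer if volunteers self-select.

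Under zero change in the non-fatigued, the pooled mean fatigue change would be 70% to 80% of that in fatigued participants. The slope could be biased either way. For adherence and value proposition, the effect is a plausible inference rather than arithmetic.

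It would go too far to say that the study could not tell a poor app from a lack of need. Baseline Chalder scores are collected from everyone, follow-up meetings ask about daily use, and a subgroup is interviewed on utility and perceived benefit. The data allow the distinction; the stated analysis does not commit to making it.

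**What to change.** Keep broad entry if that is wanted, and add to Quantitative Analysis:
- The adherence, fatigue-perception and value-proposition results will be reported by Encounter 1 Chalder score, either as a continuous variable or by a cut-off that the investigators fix before enrolment.
- Fatigued participants form the main set for the fatigue-perception objective. This requires the cut-off; the continuous form alone does not define the set.
- Baseline Chalder joins age, sex and eHEALS in the adjusted linear model, and is among the factors examined for app use.

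This takes a few sentences and no new data, visits or recruitment. The downside is smaller groups and wider intervals, as step 6 shows for 42 to 48 participants.

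Requiring fatigue at entry is an optional alternative for the investigators. It would make all 60 participants fatigued, but it needs earlier screening, limits the results to fatigued patients and narrows the study of factors associated with use. The Swiss site's admissions suggest adequate supply there (0.70 × 550 = 385 in 2019, before the other criteria, against 20 needed). The article gives no such figure for the other two sites.

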### Standardized Tools

The following is a description of the standardized tools that are used in this study. Language-appropriate and culturally validated versions will be used accordingly.

#### Expanded Disability Status Scale

The EDSS is a method of quantifying disability in MS and monitoring changes in the level of disability over time. It is widely used in clinical trials and the assessment of persons with MS [53]. The EDSS scale ranges from 0 to 10 in 0.5-unit increments that represent higher levels of disability. Scoring is based on an examination by a neurologist.

#### Quality of Life in Neurological Disorders

Neuro-QoL (Quality of Life in Neurological Disorders) is a measurement system that evaluates and monitors the physical, mental, and social effects experienced by adults and children living with neurological conditions [54].

#### Chalder Fatigue Scale

The Chalder Fatigue Scale is a self-administered questionnaire for measuring the extent and severity of fatigue within both clinical and nonclinical epidemiological populations. Although originally developed to measure the extent of chronic fatigue symptoms within clinical populations, the scale was revised and is now more widely used to measure the severity of “tiredness” rather than just chronic fatigue syndrome [47].

